### Study aim and research questions

The overarching aim of this study is to evaluate the effectiveness of the Dinosaur Child Program in reducing externalizing behavior and improving emotional and social functioning in children aged 4–8. Furthermore, the study aims to explore individual variability in intervention response and real-time parent–child dynamics using the daily diary methodology.

Specifically, the following research questions and hypotheses are addressed:

1. **Does participation in the Dinosaur Child Program lead to greater improvements in children’s emotional, social, and cognitive functioning, and reductions in externalizing behavior compared to a waitlist control group?**

*H1*: We hypothesize that children in the intervention group will show significantly more improvement in teacher- and parent-reported social, emotional, and cognitive/linguistic competencies, and significantly greater reductions in externalizing behavior than children in the control group.

2. **Does the intervention lead to reduced emotional variability and fewer daily behavior problems, as captured through daily diary methodology?**

*H2*: We hypothesize that children in the intervention group will exhibit fewer and less intense fluctuations in negative affect (controlled for mean level changes) and fewer moments of defiance, tantrums, or other behavior problems across the day, compared to the control group.

3. **Does the intervention alter day-to-day parent–child dynamics by reducing children’s experience of negative affect and promoting shared positive affect in interaction with their parents?**

*H3*: We hypothesize that children in the intervention group will show fewer escalations of negative affect and more intense shared positive moments with their parents than those in the control group. These effects are expected to be most pronounced in children who show higher baseline emotional sensitivity, operationalized as greater moment-to-moment fluctuations in negative affect prior to the intervention.

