## Materials and methods

### Study design

This protocol, which adheres to the SPIRIT 2013 guidelines (see S1 File), describes the Dino Study (Daily Intervention-based research on Nurturing Opportunities), a two-arm randomized controlled trial (RCT) designed to evaluate the effectiveness of the IY Small Group Dinosaur Child Program in Dutch children aged 4–8 years with perceived elevated or (sub)clinical levels of conduct problems [20,21,24]. A total of 120 children and one primary caregiver per family will be enrolled and randomly assigned to either an intervention group (n = 60) or a waitlist control group (n = 60), using a 1:1 ratio. The study assesses both group-level effects and individual variability in treatment response by analyzing intensive longitudinal data (ILD) from daily diaries to capture children’s moment-to-moment negative affect, externalizing behaviors, and daily parent–child interactions. The intervention group will receive the Dinosaur Child Program in small groups across 18 weekly sessions. The control group will receive care-as-usual and will be offered the intervention after posttest assessment. Pretest (T1) and posttest (T2) assessments will be conducted using standardized questionnaires and a brief child interview, with T2 scheduled 19 weeks after T1. In addition, daily diary data on children’s emotional states, behavior problems, and parent–child interactions will be collected via the m-Path application [26] during a one-week baseline period, the 18-week intervention, and a one-week follow-up (i.e., 20 weeks total). Parent and child will complete the diary jointly each evening (Fig 1). Eligibility criteria include: (a) child age between 4 and 8 years at the start of the study (September 2025), (b) parental indication that the child shows elevated or (sub)clinical levels of conduct problems in daily life (e.g., frequent defiance, aggression, or rule-breaking behavior), (c) daily contact between the child and the participating parent, and (c) sufficient fluency in Dutch. Children are excluded if they have an intellectual disability (IQ < 70) or insufficient Dutch language proficiency.

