### Data collection and procedures

A detailed overview of measures by informant and timepoint is provided in Fig 1 (SPIRIT schedule). All standardized pretest and posttest measures have demonstrated good psychometric properties. The diary items were adapted from validated instruments (e.g., PANAS-C, externalizing spectrum scales, parent-child relationships [29–32]) and tailored for daily use in young children. While validation of daily diary in early childhood is still emerging, this study contributes to ongoing efforts to evaluate ILD methods in child intervention research.

Data collection spans three phases: pre-intervention (T1), intervention, and post-intervention (T2). During T1 (September 2025), parents and teachers complete online questionnaires. The home visit includes child assent, a brief emotion regulation task, and setup of the m-Path app. From the baseline period through the 18-week intervention and one-week follow-up, daily digital assessments will be completed jointly by parent and child each evening, focusing on emotions, behaviors, and family interactions. To encourage consistent participation, families can earn up to €50 per family as incentives, distributed across key milestones: €10 for completing the pretest questionnaires, approximately €25 for daily questionnaire completion during the study period (with €0.15 per completed daily questionnaire), and €15 for completing the posttest questionnaires. Participation progress is tracked via the m-Path app, and payments will be made after study completion based on participation levels.

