#### Child emotional variability.

Emotional variability will be operationalized using parent–child dyadic daily assessments collected via the m-Path app [26]. Each evening, parents and children will complete a short diary survey including 2–3 emotion-related items (e.g., “Did your child experience strong emotions today?”) on a 5-point scale (1 = “not at all” to 5 = “very much”). Variability will be calculated based on within-person standard deviations, and changes over time will be explored using a moving window approach [28].

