#### Daily diary-based outcomes.

***Emotional variability and behavior problems (Secondary outcomes; RQ2).*** To capture within-person variability in emotional and behavioral functioning, daily diary surveys will assess both emotional functioning and behavior problems, completed each evening by the parent–child dyad using the m-Path app [26]. Emotional variability will be measured using a set of seven momentary emotion items derived from the Positive and Negative Affect Schedule for Children (PANAS-C) [29] and the original PANAS [30]. Children will indicate how they felt “at the moment” on a 7-point scale ranging from 1 (*not at all*) to 7 (*very much*), for the emotions proud, happy, calm, ashamed, sad, angry, and tense. To enhance developmental appropriateness and alignment with the Dinosaur Child Program, each response option is accompanied by a visual cue: a small-to-large image representing the intensity of each specific emotion, consistent with the emotion cue cards used during the intervention. Behavior problems will be assessed with three items reflecting hostility-related externalizing behaviors, adapted from the externalizing spectrum framework [31]. These include losing one’s patience, saying something mean to someone, and being angry or aggressive towards someone. Responses will be recorded on a 5-point Likert scale ranging from 1 (*not at all*) to 5 (*very often*), allowing for sensitive detection of daily fluctuations in child behavior over time.

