***Parent–child affective dynamics (Secondary outcomes; RQ3).*** To examine daily relational dynamics between parents and children, both members of the dyad independently complete a daily diary assessing shared emotional moments, negative interactions, emotion regulation, and time spent together. These items were adapted from validated measures of momentary relationship quality [32] and reflect shared emotional experiences, conflict-related emotions, and individual efforts at emotion regulation. This dyadic structure allows for the analysis of affective synchrony, divergence, and co-regulatory processes, which are central to understanding how the intervention impacts family functioning over time. Parents report whether they experienced nice moments with their child (“I had some nice moments with my child today.”) and whether they felt angry toward their child (“I got angry at my child today.”). These items are rated on 5-point Likert scales using either an intensity format (1 = *not at all* to 5 = *very much*) or a frequency format (1 = *not at all* to 5 = *very often*). In addition, a contextual control item is included to assess the amount of parent–child contact: “How many hours were you with your child today (excluding sleep time)?” (ranging from 0 to 24 hours). Children complete a mirrored set of items: they report whether they had nice moments with their parent, whether they got angry at their parent, how difficult it was to behave well, and what they did to manage their emotions if they felt angry. The regulation item includes a multiple-choice question offering strategies that are taught during the Dinosaur Child Program (e.g., taking deep breaths, doing the “turtle pose,” or thinking of something fun), along with an open-ended “other” option. Ratings use the same Likert formats as in the parent version to ensure comparability.

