#### Hypothesis 2: Daily variability and behavior problems (ILD-based).

To examine whether the intervention reduces children’s daily emotional variability and behavior problems, multilevel time-series analyses will be conducted on daily parent–child diary data. Daily reports will include ratings of negative affect (e.g., irritability, sadness) and behavior problems (e.g., defiance, tantrums). Repeated observations will be modeled as nested within individuals to capture both group-level trends and within-person variability over time. Fixed effects for time, group, and their interaction will be included to test for differential change trajectories across conditions. In addition, moving window techniques will be employed to capture changes in intra-individual fluctuations and identify evolving temporal patterns of variability throughout the intervention period.

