#### Hypothesis 3: Parent–child dynamics (dyadic ILD-based).

To evaluate whether the intervention enhances the emotional quality of daily parent–child interactions, multilevel time-series analyses will be applied to dyadic daily diary data. These models will examine daily reports of shared positive affect and emotional escalation during conflict, with repeated measures nested within families. Time-by-condition interaction terms will be used to assess whether trajectories of affective dynamics differ between the intervention and control groups. Moving window techniques will be used to derive fine-grained temporal indicators of affective synchrony and escalation, allowing for a dynamic examination of how relational processes evolve across the intervention period. This analytic approach offers a detailed understanding of whether the intervention promotes more stable and positive emotional exchanges between parents and children.

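### The diary is described as completed both jointly and independently, emotional variability has two incompatible definitions, and the stated H3 model lacks the baseline-sensitivity term that H3 predicts

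*Protocol article*

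**What the plan says.** **Who answers.** Study design states: "Parent and child will complete the diary jointly each evening". Data collection and procedures repeats it: "daily digital assessments will be completed jointly by parent and child each evening". Under Daily diary-based outcomes, the paragraph on parent–child affective dynamics (RQ3) says instead that "both members of the dyad independently complete a daily diary assessing shared emotional moments". It names synchrony, divergence and co-regulation as what this structure makes possible. The paragraph that follows asks whether change is felt by both members or by only one, and the Hypothesis 3 analysis derives synchrony and escalation indicators from the same data.

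**What emotional variability is.** Under Moderators, Child emotional variability describes "a short diary survey including 2–3 emotion-related items" on a 1–5 scale. Its example item asks about the child's strong emotions over the day, and the statistic is the within-person standard deviation. Under Daily diary-based outcomes, "Emotional variability will be measured using a set of seven momentary emotion items", rated by the child for the present moment on a 1–7 scale.

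**What H3 tests.** H3 has a moderation part: "These effects are expected to be most pronounced in children who show higher baseline emotional sensitivity". Sensitivity is defined there as fluctuation in negative affect before the programme starts. The Hypothesis 3 analysis states: "Time-by-condition interaction terms will be used to assess whether trajectories of affective dynamics differ between the intervention and control groups". No sensitivity term is given. The Moderators section does list emotional sensitivity among the baseline variables to be examined as predictors of differential effect.

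**The concern.** Synchrony and divergence compare two people's accounts of the same day. If parent and child answer together, part of the agreement comes from the shared sitting and not from the relationship, and the analysis cannot separate the two. The completion mode is set when the app is configured and cannot be repaired afterwards.

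The two definitions of emotional variability differ in items, scale, time frame and apparent informant. Standard deviations computed from them are not interchangeable. Neither definition, as written, isolates the negative affect that H2 and the H3 moderator name.

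For H3, a time-by-condition term estimates the average difference in trajectory. It does not show whether that difference grows with baseline sensitivity, which is what the second half of H3 asserts.

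RQ2 and RQ3 rest entirely on this diary.

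**Working it through.** **The plan's own figures.** The Power analysis section's 7 days × 20 weeks = 140 time points is correct. Its 64 and 26 per group reproduce with a two-sided two-sample t-test at α = 0.05 and power 0.80 (63.77 and 25.52, rounded up). The diary power claim (above 80% for β = 0.005) cannot be reproduced because its variance inputs are not given. The simulation is described for time by condition on rolling-window correlations, with no moderation term. This point disputes none of these figures.

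**1. Effect of joint completion on concordance.** Assume that a share c of each member's daily variance is a common component created by answering together, and that the rest carries the true correlation r. Then:

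observed correlation = (1 − c) × r + c

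observed arm difference, with the same c in both arms = (1 − c) × (r₁ − r₀)

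Take r₀ = 0.20 (control) and r₁ = 0.35 (intervention). Both these values and c are assumptions; the protocol gives none.

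| c | Control | Intervention | Difference |
|---|---|---|---|
| 0 | 0.20 | 0.35 | 0.15 |
| 0.2 | 0.8 × 0.20 + 0.2 = 0.36 | 0.8 × 0.35 + 0.2 = 0.48 | 0.12 |
| 0.4 | 0.6 × 0.20 + 0.4 = 0.52 | 0.6 × 0.35 + 0.4 = 0.61 | 0.09 |
| 0.6 | 0.4 × 0.20 + 0.6 = 0.68 | 0.4 × 0.35 + 0.6 = 0.74 | 0.06 |

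The level rises in both arms and the contrast shrinks, but it does not vanish.

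**2. The two definitions side by side.**

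| | Child emotional variability (Moderators) | Daily diary-based outcomes (RQ2) |
|---|---|---|
| Items | 2–3 | 7 |
| Scale | 1–5 | 1–7 |
| Time frame | the day (example item) | the present moment |
| Wording | about the child, in the third person | the child's own feeling |
| Valence | strong emotions, not specified | 3 positive (proud, happy, calm), 4 negative (ashamed, sad, angry, tense) |

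The largest possible standard deviation (divisor n) is half the range: (5 − 1)/2 = 2 on the first scale and (7 − 1)/2 = 3 on the second. The two are different quantities under one name. Only the four negative items of the second set match the construct in H2 and H3.

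The other 5-point scales in the diary (behavior problems, parent–child moments) belong to different constructs and are not part of the conflict.

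**3. Hypothesis against model.** H3 as worded requires condition × time × baseline sensitivity. The stated model has condition × time. The opening of Statistical analysis gives age, gender and baseline severity as example moderators and does not name sensitivity. The Moderators section names it but gives no model.

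**The case against.** **Jointly could mean in the same sitting, and independently could mean separate item sets.** The RQ3 paragraph does describe mirrored parent and child items, so two reports are intended. But the text does not draw that distinction, and a shared sitting with children aged 4–8 would not by itself keep the answers separate.

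**The moderation is planned.** This stands. A reader might infer that half of H3 goes untested, but the Moderators section commits to examining emotional sensitivity, and the exact model may sit in an analysis plan that is not shown. What remains is that the H3 model as stated does not carry the term its own hypothesis requires.

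**The moderator is defined.** This stands in large part. The concept (Introduction and H3), the window (one-week baseline, Study design) and the statistic (within-person standard deviation) are all given. Only the item set, scale and informant conflict.

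**Synchrony and sensitivity could still be tested.** This also stands. A reader might infer that neither can be validly tested. If reports are separate, as the RQ3 paragraph says, synchrony is testable. If they are joint, the contrast is diluted but not abolished. Sensitivity is testable once one item set is fixed.

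**The diary and H2.** A reader might also infer that H2 names behaviors the diary does not record, from "Daily reports will include ratings of negative affect (e.g., irritability, sadness) and behavior problems (e.g., defiance, tantrums". These are examples, sadness is among the diary items, and H2 itself extends to other behavior problems. The documents do not support that inference.

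**Parents know the arm.** This affects any parent report, joint or separate, and adds nothing to this point.

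**Conclusion.** The point holds as a matter of reconciling the text, with a real consequence for the synchrony analysis. Three things are established from the document alone: the joint/independent contradiction, the two incompatible definitions of emotional variability, and the missing baseline-sensitivity term in the stated H3 model.

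The size of the first depends on assumptions. With an equal shared component of 20% to 60% of variance, an arm difference in concordance of 0.15 falls to between 0.12 and 0.06. If sharing differed between arms, the bias could go either way; the document gives no reason to expect that. The second and third have no figure attached: they leave open which quantity is analyzed and whether the stated model answers the stated hypothesis.

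These are secondary outcomes, and no primary analysis is affected.

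**What to change.** Before the first diary (the Trial registration section says no participant had yet been recruited):

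1. Have the parent and child items for RQ3 entered separately in m-Path, and align Study design, Data collection and procedures, and Daily diary-based outcomes on this. Help given to young children will leave some dependence, which should be acknowledged when synchrony is interpreted.
2. Compute both emotional variability and baseline sensitivity from the same four negative items (ashamed, sad, angry, tense) on the 1–7 scale, and correct Child emotional variability under Moderators to match.
3. Add the condition × time × baseline-sensitivity term, with its lower-order terms, to the Hypothesis 3 model.

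The cost is app set-up, protocol wording and slightly more parent time each evening.

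Modeling sensitivity as a latent within-person variance is optional. A standard deviation from seven evenings is noisy: its simulated reliability is about 0.31, 0.49 or 0.62 if true standard deviations vary between children with an assumed coefficient of variation of 0.2, 0.3 or 0.4. That noise comes from the one-week baseline, not from the contradictions above, and the planned standard deviation remains usable.

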By collecting matched daily reports across 20 weeks of measurement, this dyadic ILD approach enables rich time-series analyses of both shared and diverging perceptions within the family. It allows the study to examine not only whether parent–child dynamics improve overall, but also whether these improvements are co-experienced and co-regulated — for example, whether decreases in child-reported anger correspond with reductions in parent-reported conflict, or whether increases in positive moments are felt mutually or asymmetrically. The inclusion of contextual time data enables the control of fluctuations in contact intensity, helping to interpret changes in affective dynamics relative to daily routines and caregiving structures.

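### The plan says the RQ3 diary items are completed both jointly and independently; joint entry would inflate parent–child synchrony and compress divergence, though not undermine H3 as a whole

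*Protocol article*

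**What the plan says.** The protocol article describes the mode of diary completion in several places.

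- Study design: "Parent and child will complete the diary jointly each evening".
- Data collection and procedures: "daily digital assessments will be completed jointly by parent and child each evening, focusing on emotions, behaviors, and family interactions". Family interactions are the content of the RQ3 items.
- Daily diary-based outcomes, RQ2 items (emotions and behavior problems): "completed each evening by the parent–child dyad using the m-Path app".
- Daily diary-based outcomes, RQ3 items (parent–child affective dynamics): "both members of the dyad independently complete a daily diary assessing shared emotional moments". The text then lists a parent set and a mirrored child set covering nice moments and anger at each other.

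The same section says what the two RQ3 reports are for: "This dyadic structure allows for the analysis of affective synchrony, divergence, and co-regulatory processes". It adds that "this dyadic ILD approach enables rich time-series analyses of both shared and diverging perceptions within the family", and gives as examples whether a fall in the child's reported anger goes with a fall in the parent's reported conflict, and whether good moments are felt by both or by one. The Hypothesis 3 analysis derives moving-window indicators of synchrony and escalation, alongside time-by-condition terms in multilevel models. RQ3 outcomes are classed as secondary.

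**The concern.** The two statements cover the same items. Joint completion cannot be confined to the RQ2 emotion and behavior items, because the Data collection section names family interactions.

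The mode matters because agreement between parent and child is itself being measured. If a child aged 4–8 and the parent rate the same evening in one conversation, some of their agreement is produced by the act of reporting. The child would also rate anger at the parent with that parent present. High synchrony or low divergence could then reflect how the pair fills in the form. The mode of entry cannot be recovered once the data are in, and families following one section would produce different data from families following the other.

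**Working it through.** **Text comparison**

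| Section | Items covered | Mode stated |
|---|---|---|
| Study design | the diary as a whole | joint |
| Data collection and procedures | emotions, behaviors, family interactions | joint |
| Child emotional variability; Daily diary-based outcomes (RQ2) | emotions, behavior problems | by the dyad |
| Daily diary-based outcomes (RQ3) | parent–child interaction | independent |

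The RQ2 rows do not conflict with the RQ3 row, since different item sets may have different modes. The conflict is between the first two rows and the last.

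**The plan's own figure.** One baseline week, 18 intervention weeks and one follow-up week give 20 weeks, and 7 × 20 = 140 time points, as the Power analysis states. No figure in the document is in dispute.

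**Illustration of the consequence.** Let ρ be the true day-to-day parent–child correlation, and k the share of each report's daily variance that is common to the reporting session. The documents give neither, so both are assumptions.

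1. Level of synchrony: observed correlation r = (1−k)ρ + k.
2. Divergence, for unit-variance reports: SD of the parent–child difference = √(2(1−r)).
3. With k equal across arms and constant over time, a true arm difference in synchrony change of Δ is observed as (1−k)Δ.

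| k | r if ρ = 0 | r if ρ = 0.20 | SD of difference if ρ = 0.20 | True Δ = 0.10 is seen as |
|---|---|---|---|---|
| 0 | 0 | 0.20 | 1.26 | 0.10 |
| 0.2 | 0.20 | 0.36 | 1.13 | 0.08 |
| 0.4 | 0.40 | 0.52 | 0.98 | 0.06 |
| 0.6 | 0.60 | 0.68 | 0.80 | 0.04 |

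Example: ρ = 0.20 and k = 0.4 give 0.6 × 0.20 + 0.4 = 0.52, and √(2 × 0.48) = 0.98.

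4. With no true change, but k falling from 0.3 to 0.2 in one arm only (ρ = 0.20), r moves from 0.7 × 0.20 + 0.3 = 0.44 to 0.8 × 0.20 + 0.2 = 0.36. That is a spurious change of −0.08. In general its size is (1−ρ) times the change in k, and its sign follows the direction of the drift.

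Levels of synchrony and divergence are therefore distorted for any k above zero. The randomized contrast is weakened when k is equal across arms and constant, and is falsely created only when k moves differently by arm.

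**The case against.** The strongest reply is that the sections may be compatible. Joint completion could mean one evening session, and independent completion could describe who answers which items. The RQ3 text does list separate parent and child items. The Study design sentence points to Fig 1, and the supporting files hold the ethics proposal and parent letters; none of these is available here. This reading is possible, but the visible text does not state it. Even under it, the reader is not told whether one member sees or hears the other's answers, and that is what the indicators depend on.

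Three further objections stand, and they limit the point.

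- A reader might infer that H3 as a whole fails under joint entry. The documents do not support that. H3 predicts fewer escalations of negative affect and more intense shared positive moments, and does not name synchrony or divergence. The analysis section starts with daily reports and time-by-condition terms. The trajectory of one informant's rating of nice moments or anger does not need a second independent report, although answers given in the other's presence may still be influenced.
- A reader might infer that joint entry would manufacture a treatment effect. That requires the shared component to drift by arm. Parents learn their allocation after baseline, only intervention families receive letters and homework, and the diary uses the program's emotion images and strategies, so drift is plausible. But nothing in the document shows it, and nothing says that parents are taught how to answer the diary.
- The outcomes are secondary. The primary questionnaires and child tasks are untouched.

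**Conclusion.** The point holds in a limited form. The plan gives two unreconciled modes of completion for the RQ3 items, and the synchrony, divergence and co-experience indicators rest on one of them. Under joint entry, agreement is overstated (for example 0.36 to 0.68 against a true 0.20, for k from 0.2 to 0.6) and divergence understated. A true arm difference in synchrony change is reduced by the factor (1−k) if k is equal across arms and constant over time. A false arm difference, such as 0.08 in size for a 0.1 shift in k in one arm at ρ = 0.20, depends on an assumed differential change. All these sizes are illustrative, because the documents give no value for k or ρ.

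The conclusion does not extend to single-informant level trajectories or to any primary outcome. It should be fixed before data collection, as a correction to a subset of secondary indicators.

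**What to change.** Reconcile the Study design, Data collection and Daily diary-based outcomes sections for the RQ3 items. State that:

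- parent and child make separate m-Path entries;
- the parent's entry is submitted and hidden before the child's opens;
- the parent's help is limited to reading out the wording;
- both time stamps are stored.

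The RQ2 emotion and behavior items may stay dyad-completed if the text says so.

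Acknowledge that, with children aged 4–8, the parent may still hear the child's answers. Separate entry reduces the shared component but does not remove it.

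If joint entry is kept for the RQ3 items, do not interpret synchrony, divergence or co-experience as separate perceptions. Drop those claims, or report them as exploratory with this limitation, and base H3 on the level trajectories.

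The cost is app configuration, wording in the protocol and parent instructions, and slightly more time each evening over up to 140 evenings. That last item matters because the Discussion already names family burden as a risk to compliance. The Trial registration section says that no participant had yet been recruited, so the change can be made before any diary data exist.
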